## Abstract

**Background:**

Osteoarthritis (OA) is a prevalent joint disorder with a need for efficient and evidence-based management strategies.

**Objectives:**

The primary purpose of this study is to compare the effects of a multidisciplinary outpatient clinic, including a brief group-based educational programme, with a traditional individual outpatient clinic for patients with hip, knee, hand or generalized OA. A secondary purpose is to investigate the effects of a telephone follow-up call.

**Methods:**

This is a pragmatic randomised single-blind controlled study with a total of 400 patients with hip, knee, hand or generalized OA between 40 and 80 years referred to an outpatient rheumatology hospital clinic. The randomisation is stratified according to the diagnostic subgroups. The experimental group is exposed to a multidisciplinary and multifaceted intervention, including a 3.5 hour group-based patient education programme about OA in addition to individual consultations with members of a multidisciplinary team. The control intervention is based on regular care with an individual outpatient consultation with a rheumatologist (treatment as usual). Primary outcomes are patient satisfaction measured at 4 months and cost-effectiveness measured at 12 months. Secondary outcomes are pain and global disease activity measured on a numeric rating scales (NRS), generic and disease specific functioning and disability using Short Form-36 (SF-36) health survey, the Western Ontario and McMaster Universities Osteoarthritis Index 3 (WOMAC), the Australian/Canadian Osteoarthritis Hand Index (AUSCAN), and a patient-generated measure of disability (Patient-Specific Functional scale, PSFS). Global perceived effect of change in health status during the study period is also reported. At 4-month follow-up, patients in both groups will be randomly allocated to a 10-minute telephone call or no follow-up ("treatment as usual"). After additional 8 months (12-month follow-up) the four groups will be compared in a secondary analysis with regard to health outcomes and health care costs.

**Discussion:**

This trial will provide results on how multidisciplinary and multifaceted management of patients with OA affects health outcomes and health care costs.

**Trial registration:**

Current Controlled Trials ISRCTN25778426

## Background

Osteoarthritis (OA) is the most prevalent joint disorder and is associated with pain, functional disability and impaired quality of life [1]. The degenerative disease process of synovial joints leads to radiographic signs and the clinical symptoms like pain, stiffness and reduced joint motion. OA is strongly associated with aging, has most commonly an onset after the age of 50 years, and is ranked as the fourth most common condition in older women and the eight most common in older men [2-4].

OA poses significant burdens in terms of reduced general health [5], work disability [6], and large societal costs which may be comparable to rheumatoid arthritis and other inflammatory diseases [7-9]. With an increasing proportion of older people in the population, OA constitutes a growing public health problem. Effective and evidence-based preventive and treatment strategies for OA are important as they may reduce both the individual burden of OA, and the economic burden to the society.

Recommendations for management of OA focus on a combination of pharmacological and non-pharmacological treatments [3,10,11]. Most of the non-pharmacological treatments have been studied in patients with hip and knee OA with a special focus on exercise, physical activity, patient education and weight control [2]. Reduced pain and improved function has been documented in patients with knee OA, and exercises and information are considered as important non-pharmacological interventions for this patient group.

Non-pharmacological management of hand OA and generalized OA has been investigated in only a few studies [12]. One recent systematic review concerning treatment of hand OA included 31 studies, most of them on the effect of pharmacological treatment [12]. Even though a few of the treatment strategies did show effect in terms of reduced pain and improved function, methodological weaknesses made direct recommendations on treatments for hand OA impossible. Various patient education programmes have been used for treating chronic health conditions, but no consensus has been reached on how patient education should be applied; either using a disease specific or generic approach, group-based or individual education, and either given by health professionals or lay tutors [13,14].

Standard treatment for OA in specialist care is an individual consultation with a rheumatologist, sometimes followed by referral to one or several other health professionals. However, many patients with OA experience this provision of health services as fragmented. Due to an increasing demand for a more coordinated approach, a pilot multidisciplinary OA outpatient clinic was established at Diakonhjemmet Hospital, Oslo, Norway, in 2003. The multidisciplinary team included rheumatologists, nurses, health secretaries, occupational therapists, physical therapists, pharmacists, orthopaedic surgeons and a dietician. Over a two year period, approximately 300 patients with OA were referred to the OA clinic by their general practitioners or specialists. Of these 300, 73 patients were followed for 1 year [15]. Most (78%) of these patients were women (mean age 61 years (range 24-92)). More than 60% reported to have pain in their knees and/or hands, while 40% had pain primarily localized to the hip. Approximately one fourth of the patients used NSAIDS and/or other types of analgesics. At the one year follow-up, 95% of the patients were very satisfied with the team care received, and pain and functioning was moderately improved [15]. This first evaluation with an open longitudinal design without a control group warranted the need for a more systematically and thorough evaluation of the effect and cost-benefits of this multidisciplinary, coordinated outpatient OA clinic.

The number of referrals to the clinic increased in the pilot period. To meet patients' need for information, a brief group-based educational programme was developed. Thus, in the updated multidisciplinary OA clinic, starting from 2005, patients first receive a 3.5 hours group education. After a lunch brake, they have individual consultations with a rheumatologist and thereafter, dependent on identified needs, also have encounters with other health professionals.

Few other studies have evaluated the effect of group-based educational programmes for OA in combination with a pragmatic individual approach, especially in a setting of a randomised clinical trial (RCT) [13].

The purposes of this study are 1) to compare the effect of a multidisciplinary outpatient clinic, including a brief group-based educational programme, with a regular care individual outpatient clinic for patients with hip, knee, hand and/or generalized OA, and 2) to compare the effect of a telephone follow-up call with follow-up "as usual" for patients with hip, knee, hand and/or generalized OA.

### Hypotheses

1) Patients with hip, knee, hand and/or generalized OA who receive a multidisciplinary and multifaceted intervention will be more satisfied with the health service at 4-month follow up compared to patients who receive individual consultation(s) in a regular care individual outpatient clinic.

2) The multidisciplinary and multifaceted outpatient clinic will reduce the use of health services and thus, this intervention will be more cost-effective at 12-month follow up than the traditional individual outpatient clinic.

3) Patients who receive a telephone call after 4 months will at 12-month follow-up report more satisfaction with the health service than those within the same group allocation who do not receive any telephone follow-up.

4) At 4- and 12-month follow-up, changes in the secondary outcomes VAS pain, global disease activity, generic and disease specific functioning and disability (measured by SF-36, WOMAC and AUSCAN) will not be different between patients who are managed in a multidisciplinary outpatient clinic and patients who receive regular care in a traditional individual outpatient clinic.

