### Data analysis

#### Power calculations

As no satisfactory data on patient satisfaction and cost-effectiveness were available, power calculations were based on the secondary outcome pain with data from the pilot study and previous research on OA from our group [26-28]. In this RCT we compare two independent equally sized groups. We assume comparable variation in both groups, set alpha to 5%, beta to 80%, and assume a smallest clinical important difference between the groups of 0.20 based on an estimated difference for pain measured by WOMAC/AUSCAN. The standardized difference (0.20)/SD (0.70)) will be 0.25. According to the Altman nomogram, approximately 200 patients will be needed in each of the two treatment groups.

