#### Statistical analyses

Primary data analysis will be performed in a blinded manner, by conducting the effect analyses without knowing which intervention each of the two groups received. The treatment groups will be examined for baseline comparability. Both parametric and nonparametric statistical analyses will be used, dependent on how the variance is distributed. Effect of the interventions will be analyzed according to intention-to treat principles. Further, exploratory analyses will be performed to study the treatment effect within the three subgroups hip, knee and hand OA.

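### Hypothesis 4 predicts no difference in health outcomes, but the trial is sized to detect one and gives no margin or criterion for supporting the prediction

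*Protocol article*

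**What the plan says.** Three places in the protocol article bear on this.

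- **Hypotheses, no. 4.** At 4 and 12 months, changes in VAS pain, global disease activity, and functioning and disability (SF-36, WOMAC, AUSCAN) "will not be different between patients who are managed in a multidisciplinary outpatient clinic and patients who receive regular care".
- **Power calculations.** Because satisfactory data on satisfaction and cost-effectiveness were lacking, "power calculations were based on the secondary outcome pain with data from the pilot study" and earlier work by the group. The authors "assume a smallest clinical important difference between the groups of 0.20 based on an estimated difference for pain measured by WOMAC/AUSCAN", with SD 0.70, and arrive at about 200 patients per group.
- **Statistical analyses.** "Both parametric and nonparametric statistical analyses will be used, dependent on how the variance is distributed". The effect analyses follow intention to treat and are run without knowing which group is which. No test is named.

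Under Secondary outcomes, WOMAC is given to hip and knee patients and AUSCAN to hand patients. Pain is also measured separately on a 0–10 numeric scale.

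**The concern.** A prediction of no difference needs a statement of how large a difference would still count as none, and a rule for deciding that the data exclude anything larger. The article has neither. What it does have is a calculation for the opposite purpose, finding a difference of 0.20 if one exists. So two stated parts of the article pull apart: the hypothesis expects equality, and the design is built to detect inequality.

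Without a criterion, the easiest reading of a non-significant result is that Hypothesis 4 has been borne out. Small samples, missing questionnaires and noisy scales all make non-significance more likely, so weaker data would appear to give stronger support. A difference that the plan itself calls important could then be reported as absent.

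**Working it through.** **Inputs.** Difference 0.20, SD 0.70, alpha 5%, equal groups and about 200 per arm come from Power calculations. Two assumptions are mine: the test is two-sided, and the printed beta of 80% means power of 80%. Normal approximation throughout.

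**1. The plan's own figure.** n = 2[SD(z₀.₉₇₅ + z₀.₈₀)/difference]² = 2[0.70 × (1.960 + 0.842)/0.20]² = 193 per arm. Power at 200 per arm is 81.5%. The stated 200 is therefore a sample size for detecting a difference. (The printed standardized difference of 0.25 does not equal 0.20/0.70 = 0.286 and would need 252 per arm. That is a separate matter.)

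**2. What a non-significant result leaves open.** SE = 0.70 × √(2/200) = 0.070.

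- The difference test is non-significant when the observed difference is below 1.96 × 0.070 = 0.137 in size.
- The 95% interval excludes 0.20 only when it is below 0.20 − 0.137 = 0.063.
- The 90% interval excludes 0.20 only when it is below 0.20 − 1.645 × 0.070 = 0.085.

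Observed differences from about 0.063 to 0.137 are thus non-significant and still compatible, by the 95% interval, with the plan's smallest important difference. This is not a rare zone. If the true difference is 0, the test is non-significant with probability 0.95, but the 95% interval lies inside ±0.20 with probability 0.63. The gap is 0.95 − 0.63 = 0.32.

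**3. Non-significance under real differences.** P(non-significant) ≈ Φ(1.96 − true difference/0.070):

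| True difference | P(non-significant) |
|---|---|
| 0.20 | 18.5% |
| 0.15 | 43% |
| 0.10 | 70% |

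**4. Equivalence power.** The article gives no margin, so I assume ±0.20, with two one-sided 5% tests (the 90% interval) and true difference 0. Power = 2Φ(0.20/SE − 1.645) − 1.

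| Analysis | Per arm | SE | Power |
|---|---|---|---|
| WOMAC and AUSCAN pain pooled, all 400 | 200 | 0.070 | 77.5% |
| WOMAC alone | 133 | 0.086 | 51% |
| AUSCAN alone | 67 | 0.121 | about 1% |

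The last two rows assume equal thirds for hip, knee and hand (200 × 2/3 and 200/3) and SD 0.70 for each instrument. For AUSCAN the 90% half-width is 1.645 × 0.121 = 0.199, so almost no observed difference could qualify. The chance that a difference test misses a true 0.20 is 36% for WOMAC and 62% for AUSCAN.

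**5. Sample size for 80% equivalence power, pooled.** n = 2[0.70 × (1.645 + 1.282)/0.20]² = 210 per arm with the 90% interval, or 258 with the 95% interval. Non-inferiority with the same margin at one-sided 2.5% needs 193.

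**The case against.** The defence has several sound points.

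- **Nothing says that non-significance will be read as equality.** A reader might infer that it will, since no other criterion is given. But Statistical analyses names no test and does not exclude confidence intervals, so that intention cannot be attributed to the authors. A missing decision rule alone could also be left to a fuller document. What stands is the mismatch between a stated hypothesis of no difference and a stated sample-size basis for a difference.
- **A reader might infer that the satisfaction and cost conclusions rest on Hypothesis 4.** Formally they do not. Hypotheses 1 and 3 use the satisfaction scale. Cost-effectiveness uses EQ-5D utilities and costs, and EQ-5D is not among the outcomes in Hypothesis 4.
- **The 0.20 and SD 0.70 belong to WOMAC/AUSCAN pain.** Hypothesis 4 names VAS pain, for which the article gives neither an SD nor an important difference. The figures above do not carry over to that scale or to the other outcomes.
- **The 18.5% is simply the type II error of a design with roughly 80% power.** That is correct. It becomes a problem only where the miss would count in favour of a hypothesis.
- **The sample size is not far off.** For a pooled pain score, 200 against 210 is a small shortfall, and a non-inferiority reading would be covered before dropout. But this depends on a pooling rule that the article does not state.

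These points limit the size of the finding. They do not remove it.

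**Conclusion.** The point holds as a should-fix. As described, the design cannot support Hypothesis 4: the sample size is for detecting a difference, there is no margin or criterion, and a non-significant result leaves the plan's own important difference open whenever the observed difference lies between about 0.063 and 0.137 (200 per arm, SD 0.70, 95% interval).

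The equivalence figures rest on a margin that I took from the plan's smallest important difference, a true difference of 0, full follow-up and a single time point. The separate-instrument figures also assume equal thirds. The prediction covers both 4 and 12 months, so requiring equivalence at both could only lower the power.

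The consequence is confined to what may be said about secondary health outcomes.

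**What to change.** Choose one of two routes and align Hypotheses, Power calculations and Statistical analyses with it.

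1. **Drop the prediction of no difference.** Report each between-group difference with its confidence interval, and state that a non-significant result is not evidence of equality.
2. **Keep it for WOMAC/AUSCAN pain only, as equivalence.** Claim no difference only if the 90% interval lies within ±0.20, and otherwise report the result as inconclusive. State whether the two instruments are pooled. For VAS/NRS pain and the other outcomes, either fix and justify a margin before unblinding, and preferably before the masked effect analyses are run, or make no such claim.

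If equivalence power is stated, its assumptions should stand beside it: about 78% only for a pooled pain score in all 400 patients with full follow-up, SD 0.70 and true difference 0. Analysed separately with equal thirds, it is about 51% for WOMAC and about 1% for AUSCAN. Quoting 78% alone would mislead.

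The cost is wording and an interval rule, with no extra patients. The downside is that some results will be reported as inconclusive, and AUSCAN pain analysed alone would almost always be.

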## Methods

Patients are randomised into the two interventions within three strata: patients with primary hand, hip or knee problems. A project coordinator includes patients and coordinates the patient-reported data collection with questionnaires. Health professionals who are taking part in the two interventions are not involved in the data collection. Blinding of providers and patients is not possible in this type of study, but the outcome assessors as well as those who perform the follow up telephone call are blinded. All patients involved in the project have signed an informed consent and have been informed according to the Helsinki declaration. The data inspectorate and the regional ethical committee (REK) reviewed and approved the project (REK ref 156-06073 1.2006.598); the ISRCTN trial number is 25778426.

### Study sample and setting

A total of 400 participants referred to an outpatient hospital rheumatology clinic with a diagnosis of hip, knee, hand and/or generalized OA, will be recruited for the study.

### Subjects

To be eligible for inclusion, participants must be between 40 and 80 years and have a clinical diagnosis of hip, knee, hand and/or generalized OA confirmed by a specialist. The eligibility criteria are described in Table 1.

**Table 1 T1:** Eligibility criteria

Inclusion criteria	Exclusion criteria
Clinical diagnosis osteoarthritis	Recent surgery
Referral from general practitioner or specialist	Cognitive impairments
40-80 years	Inability to read and understand Norwegian
	Recent trauma in the extremities, other known or relevant co-morbidities such as rheumatoid arthritis and cancer

### Primary intervention

The *experimental intervention *is a multidisciplinary and multifaceted intervention, in which the referred patients first receive a 3.5 hour group-based educational programme, and thereafter individual consultations with a rheumatologist and other members of the multidisciplinary team, dependent on identified needs. The multidisciplinary team consists of rheumatologists, an orthopaedic surgeon, nurses, health secretaries, physiotherapists, occupational therapists, a pharmacist and a dietician.

The group-based educational programme contains four main themes identified through qualitative interviews with patient advocates. The themes are: a) What is OA? b) Activity possibilities or limitations, what can we do ourselves? c) Treatment options and d) How to live with OA.

The *control intervention *is regular care in an individual outpatient clinic. The patients are referred to and examined by a rheumatologist. According to usual procedures they are referred to other specialists or health professionals such as orthopaedic surgeons, physiotherapists, occupational therapists etc. dependent on identified needs. The access to health care providers is in principle similar to the access in the experimental group, but encounters occur according to referral.

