### Group allocation

All patients are randomly allocated to one of two groups, experimental or control group. This randomisation is performed after completion of the baseline questionnaires. To ensure equal-sized treatment groups, random permuted blocks of 4-8 participants are used [17]. The stratified random allocation schedule is computer generated by a statistician who is not otherwise involved in recruitment, assessment or treatment of participants. The randomisation sequence is carried out in sequentially numbered, opaque, sealed envelopes.

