### Baseline questionnaire

All patients are asked to fill in a questionnaire at inclusion, containing information on socio-demographics (age, gender, height, weight, marital status, work situation, emotional distress and physical activity), earlier and current pharmacological and non-pharmacological treatment for their OA and co-morbidities. They are also asked to complete standardised instruments for measurement of pain; functioning and health related quality of life.

Additional therapies and co-interventions are also registered. Patients who withdraw from the study will be registered by a research secretary. Delivery of interventions in both groups will be registered by the health professionals responsible for the intervention. Registering co-interventions will be part of the diary.

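### The sample size makes no allowance for group-delivered education in one arm only, and the article fixes no session-level analysis

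*Protocol article*

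**What the plan says.** All places are in the Protocol article.

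- **Group allocation:** the patient is the unit of randomisation. "All patients are randomly allocated to one of two groups, experimental or control group", in permuted blocks of 4 to 8.
- **Primary intervention:** the experimental clinic is one "in which the referred patients first receive a 3.5 hour group-based educational programme", followed by individual consultations according to need. The control intervention "is regular care in an individual outpatient clinic". No group component is described for it.
- **Background:** in the updated clinic the education comes first, and the individual consultations follow after lunch.
- **Power calculations:** "In this RCT we compare two independent equally sized groups. We assume comparable variation in both groups". With a difference of 0.20 and an SD of 0.70 for WOMAC/AUSCAN pain, a nomogram gives about 200 per arm. No design effect is mentioned.
- **Statistical analyses:** parametric or nonparametric methods, by intention to treat. No model is named and the education sessions are not mentioned.
- **Baseline questionnaire:** "Delivery of interventions in both groups will be registered by the health professionals responsible for the intervention". The section does not say whether the particular session is identified.

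**The concern.** Patients taught together share peers, a date and the way that session went. Their outcomes may therefore be more alike than those of patients from different sessions. Control patients have no such shared session. Session-level variance then enters one arm only, and it falls on the contrast that the trial tests.

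The first primary outcome, satisfaction with the health service, is plausibly sensitive to how a session was run. Two things are at stake:

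- the power of the trial, because the sample size leaves this variance out;
- the validity of the standard error, if the analysis leaves it out too.

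A later analysis plan can choose a suitable model, but it cannot recover session membership that was never recorded. The Time schedule section says that data collection is ongoing.

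**Working it through.** **Inputs from the article.** Difference 0.20, SD 0.70, alpha 5%, 200 per arm. The printed beta of 80% is read as power of 80%. The test is taken as two-sided, which the article does not state.

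**Inputs assumed.** The article gives neither session size nor ICC. I take m = 6 to 12 trial patients per session and ICC = 0.01 to 0.10. Total variance is held equal in the two arms, with the ICC as the session share of it in the experimental arm.

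**Step 1: reproduce the stated size.** With independent patients, n = 2 × (1.960 + 0.842)² × (0.70/0.20)² = 2 × 7.849 × 12.25 = 192.3, so 193 per arm (194 with the t distribution). Power at 200 per arm is Φ(0.2857 × √(200/2) − 1.960) = Φ(0.897) = 81.5%. This matches about 200 per arm and 80% power, and it contains no design effect.

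The printed standardised difference of 0.25 does not equal 0.20/0.70 = 0.286. At 0.25, two-sided, 252 per arm would be needed, and power at 200 would be 70.5% before any clustering. That is a separate inconsistency; 0.286 is used below.

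**Step 2: slack.** With clustering in one arm, n = (1 + DE) × 7.849 × 12.25 = (1 + DE) × 96.15, where DE = 1 + (m − 1) × ICC. Setting n = 200 gives 1 + DE = 2.08. The stated size therefore keeps 80% power only while DE is at most about 1.08. For example, m = 8 with ICC 0.01 gives DE = 1.07.

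**Step 3: effect of clustering.**

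- Variance of the difference: SD² × (DE + 1)/n, against 2 × SD²/n if sessions are ignored. The variance ratio is R = (1 + DE)/2.
- True size of a nominal 5% test that ignores sessions: 2Φ(−1.960/√R).
- Power of a correctly calibrated test at 200 per arm: Φ(0.2857/√((1 + DE)/200) − 1.960).

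| m | ICC | DE | R | SE ratio √R | True size if ignored | Power, pain |
|---|---|---|---|---|---|---|
| any | 0 | 1.00 | 1.000 | 1.000 | 5.0% | 81.5% |
| 6 | 0.01 | 1.05 | 1.025 | 1.012 | 5.3% | 80.6% |
| 10 | 0.01 | 1.09 | 1.045 | 1.022 | 5.5% | 79.8% |
| 10 | 0.05 | 1.45 | 1.225 | 1.107 | 7.7% | 73.3% |
| 12 | 0.10 | 2.10 | 1.550 | 1.245 | 11.5% | 63.1% |

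For m = 10 and ICC 0.05, (1 + 1.45)/200 = 0.01225, whose square root is 0.1107. Then 0.2857/0.1107 = 2.581, and Φ(2.581 − 1.960) = 73.3%. A nominal 95% interval that ignores sessions would cover about 92.3%.

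**Step 4: what carries over.** The power column belongs to pain, the only outcome that the article powers. For a given m and ICC, the SE ratio and the true size apply to any mean contrast, including satisfaction. These are large-sample figures. With 200 experimental patients and m = 10 there are about 20 sessions, so the limited number of sessions matters as well.

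**The case against.** A reader might infer that the planned analysis treats all patients as independent, that its confidence intervals are too narrow and that its type I error is inflated. The article does not support this. The Statistical analyses section names no model, and a mixed model with a session effect would count as a parametric analysis. The model may be set out in an analysis plan that is not shown. The phrase "In this RCT we compare two independent equally sized groups" describes unpaired arms; it says nothing about independence of patients within an arm. "We assume comparable variation in both groups" is an input to the sample size and is not stated as an assumption of the analysis. Nor does the article say that the same staff run a whole session.

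The effect may also be small. The shared exposure is one 3.5-hour session followed by individual consultations, and satisfaction is measured at 4 months, so a low ICC is credible. What counts is the number of trial patients per session. The programme has been part of the clinic since 2005, and the article does not say that sessions are limited to trial participants. If they are mixed, m falls. Clustering by clinician may exist in both arms, so a session effect in one arm is not the only possible structure.

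All of this stands, and it makes the consequences for the intervals and the test conditional. It does not touch the sample size, which is printed with its assumptions and is reproduced only without a design effect. Nor does it show that session membership will be recorded.

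**Conclusion.** The point holds in a limited form. It is established that grouped delivery occurs in one arm of an individually randomised trial, that the sample size of about 200 per arm contains no allowance for it, and that the slack covers a design effect of only about 1.08 in that arm.

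It is conditional that the standard error will be understated: this requires an analysis that ignores sessions and an ICC above zero. Over the assumed ranges the understatement runs from negligible (about 1% in the standard error) to material (about 25%), with 11% in the central case. With an ICC of zero nothing changes. The fall in power from about 81% to 73% applies to pain at 0.20/0.70 and must not be read as a figure for satisfaction or cost-effectiveness.

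**What to change.** 1. Record the session date or an identifier for every experimental patient, as part of the delivery registration described under Baseline questionnaire.
2. Analyse the satisfaction and cost-effectiveness contrasts with a partially nested mixed model: a random session effect in the experimental arm, arm-specific residual variances and a small-sample degrees-of-freedom correction. Cluster-robust standard errors with a small-sample correction are an acceptable alternative. In any bootstrap of costs and utilities, resample sessions in the experimental arm.
3. In Power calculations, restate power as a range over plausible session sizes and ICCs, and say that it refers to pain. This does not require enrolling more patients.

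The cost is one data field, a different model and possibly slightly wider intervals. Because a session identifier reveals the experimental arm, the model should be fixed in writing before the analysis, which the article plans to run without knowledge of allocation.
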